### Interim analysis and Data and Safety Monitoring Board

An unblinded statistician will conduct an interim efficacy analysis on the primary outcome of 30-day readmission rates once 50% of patients have been accrued in the trial and have 30-day outcomes. We will use the Haybittle-Peto procedure with a large critical value (*z* score ±3.0, two-sided α = 0.0027) [24]. Given the single planned interim analysis, no adjustment to the final critical value is needed [24]. At the same time, we will also conduct a futility analysis in which we will estimate the conditional power under the null hypothesis of no difference and the designed alternative of 30% reduction in the 30-day readmission rate. Conditional power is the probability of detecting a difference at the end of the study (*p* < 0.05), given the data trends at the time of the analysis. A recommendation will be made to stop the study for futility if the conditional power is less than 0.10. In addition to the interim efficacy and futility analyses, a sample size reestimation will also be conducted that is based on the overall readmission rate and the rate of dropouts from the intervention group, The DSMB will be composed of a senior biostatistician and three clinicians who are not affiliated with the research team. The DSMB will make recommendations to the study’s principal investigator and an executive steering committee with oversight of the evaluation.

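### Conditional power for futility counts a significant difference in either direction, so if the null-based value governs the 0.10 threshold, or both values must fall below it, a clearly adverse interim trend does not meet the rule

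*Protocol article*

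**What the plan says.** All of this stands in the protocol article, section Interim analysis and Data and Safety Monitoring Board.

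- Timing: one look, "once 50% of patients have been accrued in the trial and have 30-day outcomes".
- Efficacy boundary: symmetric, z "score ±3.0, two-sided α = 0.0027". The final critical value is left unadjusted.
- Futility calculation: "we will estimate the conditional power under the null hypothesis of no difference and the designed alternative of 30% reduction" in the 30-day readmission rate.
- Definition: "Conditional power is the probability of detecting a difference at the end of the study (*p* < 0.05), given the data trends" at the interim.
- Decision: "A recommendation will be made to stop the study for futility if the conditional power is less than 0.10".

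The definition has no direction. The decision sentence speaks of a single conditional power, although two have just been named.

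**The concern.** A futility rule should ask whether the trial can still show what it set out to show, which here is fewer readmissions. A definition that counts any significant difference also counts the opposite result. Under the null assumption this makes conditional power symmetric in the interim z: the further the interim result moves towards harm, the higher the value climbs, because significant harm becomes likelier.

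If the null-based value governs, the rule would recommend stopping a trial that shows nothing but not one in which the program looks clearly worse. If both values must be below 0.10, it would stop for a mildly adverse trend but not for a stronger one.

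An adverse measured trend is not far-fetched. The Discussion's limitations expect intervention patients to come back more readily to the system's own hospitals, the only ones where readmissions are counted. Patients are also randomized under a consent waiver (Ethics).

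**Working it through.** **Inputs.** From Sample size: usual care 20%, transition services 14%, 80% power, α = 0.05, total 1230, raised to 1520 (760 per arm) for 10% non-participation. From the interim section: information fraction t = 0.5, interim boundary ±3.0, futility threshold 0.10, final critical value unadjusted (taken as 1.96). I take 380 per arm at the interim. Positive z means benefit.

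**The plan's own figures reproduce.**
- Two-sided 0.05, 80% power, 20% vs 14%, no continuity correction: 615 per arm, total 1230.
- Dilution: 1230 / 0.9² = 1518.5, about 1520.
- 2 × (1 − Φ(3)) = 0.0027.

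**Formula.** Given interim z, the final Z is normal with mean z√t + θ(1 − t) and variance 1 − t. Without direction, CP = P(Z > 1.96) + P(Z < −1.96). The expected final Z, θ, is:
- null: 0
- designed effect: 0.06 / √[(0.20×0.80 + 0.14×0.86)/760] = 3.12
- diluted effect, 0.9×14% + 0.1×20% = 14.6%: 0.054 / √[(0.20×0.80 + 0.146×0.854)/760] = 2.79

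**Example, z = −2, null.** Mean −2 × 0.7071 = −1.414, SD 0.7071. Harm tail: Φ((−1.96 + 1.414)/0.7071) = Φ(−0.77) = 0.220. Benefit tail: 0.000.

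| Interim z | Rate vs 20% | CP, null | CP, 14% | CP, 14.6% |
|---|---|---|---|---|
| 0 | 20.0% | 0.006 | 0.287 | 0.212 |
| −1 | | 0.038 | 0.059 | 0.036 |
| −1.49 | 24.5% | 0.100 | 0.020 | 0.012 |
| −2 | 26.1% | 0.220 | 0.007 | 0.006 |
| −2.99 | about 29.4% | 0.586 | 0.024 | 0.040 |

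Rates come from a pooled two-proportion z with 380 per arm and 20% under usual care. At z = −2 the excess is 380 × 0.061, about 23 readmissions.

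**Where the rule CP < 0.10 is met, without direction.**
- Null value governs: −1.49 < z < 1.49.
- Designed alternative governs: −3.70 < z < −0.72 (14%) or −3.46 < z < −0.48 (14.6%).
- Both must be low: only −1.49 < z < −0.72 (or −0.48). A flat result does not meet the rule on this reading.
- Either suffices: from −3.70 (or −3.46) up to 1.49, with no gap.

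**Chance that the interim falls in −3 < z ≤ −1.49:** 0.07 if the true transition services rate is 20%, 0.20 if 22%, 0.39 if 24%.

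**Counting benefit only.** The rule is met for every z < 1.49 (null), z < −0.72 (14%) or z < −0.48 (14.6%).

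**The case against.** The strongest reply is that one of the two named calculations behaves properly. Under the designed 30% reduction an adverse trend lowers conditional power: it is 0.006 to 0.007 at z = −2 and stays below 0.10 through −3. This stands. A reader might infer that an adverse trend raises conditional power whatever effect is assumed; the plan's own second calculation shows otherwise. The anomaly depends on which value the threshold governs, and the plan leaves that open.

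A reader might also take the words about data trends to mean that the observed trend is projected forward, which would give 0.89 at z = −2. The text names two assumed effects and the current trend is not one of them. The phrase can simply mean conditional on the interim data, so I place no weight on that figure.

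A third inference would be that z = −3 is the only ground for stopping for harm. The article does not say so. The board sees unblinded data (Randomization and blinding), it makes recommendations, and missing the futility threshold does not oblige it to continue. Its charter is not shown, so the absence of a separate harm rule here is no finding.

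Finally, the sponsor may have meant benefit only, with the formula set out elsewhere. That is plausible, since the designed effect is a reduction. But the article states a definition, a threshold and a decision, and taken together they do not say this.

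**Conclusion.** The point holds in a limited form. The stated definition has no direction, and the threshold is not tied to one of the two calculations. If the null-based value governs, or both must be below 0.10, an interim result with −3 < z ≤ −1.49 has null-based conditional power between 0.10 and 0.59, all from significant harm, and does not meet the futility rule. If the designed alternative governs, or if either value suffices, there is no anomaly inside ±3.

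The open choice of assumed effect matters at least as much. At z = 0 the null value is 0.006 (stop) and the designed-alternative value is 0.21 to 0.29 (continue).

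The figures assume exactly half the information, 380 analysed per arm, 20% readmission under usual care, a final critical value of 1.96, and the normal approximation in place of the logistic model. A sample size re-estimation at the same look would change the information fraction and shift the cut-offs.

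**What to change.** In the interim section, define conditional power as the probability that the final analysis shows a significantly lower 30-day readmission rate with transition services (final Z beyond 1.96 in that direction). Apply the 0.10 threshold to that quantity, and name the assumed effect that governs it.

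The second choice needs thought. With the null governing, a benefit-only rule also recommends stopping for favourable trends up to z = 1.49. The expected interim z under the design is 3.12 × √0.5 = 2.21, or 2.79 × √0.5 = 1.97 after dilution. A trial whose design assumption is true would therefore meet the rule with probability Φ(1.49 − 2.21) = 0.24, or Φ(1.49 − 1.97) = 0.31. With the designed alternative governing (cut-off −0.72 or −0.48), the same probability is Φ(−0.72 − 2.21) or Φ(−0.48 − 1.97), both below 0.01.

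The cost is a sentence or two and no patients. A one-directional rule, if non-binding, does not raise the type I error for benefit. The small downside is that a program trending adverse may be stopped before harm is formally significant.

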### Ethics

The trial was approved by the Carolinas HealthCare System Institutional Review Board and granted a waiver for patient consent (reference number 01-15-10E).

## Discussion

The AIRTIGHT trial will provide important information to healthcare systems that currently have little evidence-based guidance for efforts to improve readmission rates and avoid financial penalties. First, though some trials have suggested that multifaceted interventions have potential benefit, others have suggested no benefit [6–8, 20, 22]. AIRTIGHT is the first U.S. randomized study within a large, integrated healthcare delivery system to examine the effectiveness of an intensive intervention that bridges the pre- and postdischarge periods while incorporating the most recent recommendations for hospital transitions, virtual care, and dedicated paramedicine providers. Second, the pragmatic design of this study will create information that is generalizable to other healthcare systems. We have intentionally applied the PRECIS-2 tool to match the study design to how the evidence is intended to be implemented [13]. Although randomizing patient referrals with limited inclusion and exclusion criteria increases the risk of effect-size attenuation and the study being underpowered, there is significant benefit for stakeholders to have a clear understanding of the potential reach and real-world effectiveness of the intervention. Third, the methods of the AIRTIGHT trial provide a template for healthcare systems to conduct quality improvement research that fits seamlessly into existing care delivery and quality improvement efforts. To ensure both the relevance of the questions asked and the seamless integration of the trial into clinical workflows, we formed an executive steering committee. The executive steering committee includes representation from healthcare system senior leadership and each of the major disciplines involved in the transition services program.

As the paradigm of healthcare delivery continues to evolve rapidly, the imperative increases for healthcare systems to have real-time, reliable information upon which to act. These methods should be leveraged to guide continuous improvement, strategic decisions, and investments that are necessary to transform care and value for patients.

This study has several potential limitations. First, although there are few exclusion criteria, generalizability could be threatened by the study being contained within one healthcare system. Despite this, patients are expected to be broadly representative of the general population that is at high risk for readmission because of the racially, ethnically, and geographically diverse population served by this healthcare system. Second, because we do not have access to payer-level claims data, outcomes analysis is limited to the 30 hospitals contributing clinical data to the study. If a difference in rates of hospitalization outside these 30 hospitals exists between groups, it would be expected to bias the results toward the null. Such a difference is expected because the intervention group participants should be more likely to return to the sponsoring health system’s hospitals owing to the ongoing contact with transition services personnel. Third, given the complex nature of the transition services intervention, we will not be able to isolate the effects of individual intervention components. Transition services is designed to encompass the current literature recommendations for a multifaceted intervention with the expectation that health systems would look to replicate the intervention and not its subcomponents. However, to provide an additional layer of understanding of both the intervention’s components and its implementation, a separate qualitative study will be conducted.

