### Outcomes

The primary outcome is the rate of 30-day, nonelective readmissions to any of the 30 hospitals affiliated with the sponsoring healthcare system. We followed the definition for nonelective readmissions as set out by the Centers for Medicare and Medicaid Services (CMS); however, we included both inpatient and observation classifications to create an outcome that is more patient-centered (Fig. 3). To allow for nondifferential outcome assessment, we use only data that are collected and available as part of routine care. Secondary outcomes include the 30-day nonelective readmission rates separated by inpatient and observation classifications (Fig. 3), 30-day emergency department use, 30-day acute care use composite (primary outcome of readmission plus emergency department use), 60- and 90-day readmission rates (using primary outcome definition of readmission), and length of stay on index and readmission visit. Additionally, in cost analysis, we will compare the total patient charges at 30, 60, and 90 days across groups with modeling of cost inclusive of estimated readmission penalties. To provide an understanding of implementation factors, RE-AIM measures are reported to the care team through monthly automated reports (Table 2) [18]. Because this evaluation is also designed to inform a quality improvement project, we expect that the clinical team may use the RE-AIM measures to adapt the transition services program during the course of the evaluation. Any substantial changes in process, procedures, or services will be documented and incorporated into the outcome analyses.

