### Analysis

All analyses will follow intention-to-treat principle such that patients will be analyzed on the basis of the group to which they were initially randomized, but after reapplication of inclusion and exclusion criteria at the time of hospital discharge (Fig. 1, “Eligible at discharge” bubble). Baseline comparisons of the two groups will be made using univariate analyses such as the *t* test and chi-square test. The primary outcome, readmission in 30 days, will be compared between the two groups of patients who are eligible at discharge, using logistic regression. Results will be presented with ORs and 95% CIs. In addition to the intention-to-treat analysis, we will perform a per-protocol analysis to evaluate the patients who are eligible at discharge and participate in the transition services program compared with usual care patients who are eligible at discharge. For all outcomes, we assume that if there are no visits in the electronic medical record, the value for having a visit is null; therefore, there will be no missing data for the primary or secondary outcome measures.

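### More complete capture of readmissions in the intervention arm biases against the intervention, not unconditionally toward the null as the Discussion states

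*Protocol article*

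**What the plan says.** Four statements bear on this point.

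- **Outcomes** defines what is counted: "The primary outcome is the rate of 30-day, nonelective readmissions to any of the 30 hospitals affiliated with the sponsoring healthcare system". It adds: "To allow for nondifferential outcome assessment, we use only data that are collected and available as part of routine care".
- **Analysis** sets the coding rule for all outcomes: "we assume that if there are no visits in the electronic medical record, the value for having a visit is null". It concludes: "therefore, there will be no missing data for the primary or secondary outcome measures".
- **Discussion**, limitations paragraph, gives the boundary of what can be seen: "because we do not have access to payer-level claims data, outcomes analysis is limited to the 30 hospitals contributing clinical data to the study".
- The same paragraph says of a between-arm difference in outside hospitalization that "it would be expected to bias the results toward the null". It then says that the difference is anticipated: "Such a difference is expected because the intervention group participants should be more likely to return" to the system's own hospitals, because of their continuing contact with program staff.

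**The concern.** A readmission outside the 30 hospitals is scored zero. If intervention patients come back to the system more often, a larger share of their readmissions is counted, and their observed rate is raised relative to control. The direction of that bias is fixed: it is against the intervention. Whether this is also toward the null depends on the truth, which the trial is there to find out. For a program that works, it attenuates the benefit. For a program with no effect, it creates an apparent excess of readmissions. For a harmful one, it exaggerates the harm. The no-effect case is realistic, since the Background and Discussion both cite trials that found no benefit.

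At stake is how a null or adverse result is read. A reader who relies on the stated direction would take apparent harm as real, or even as understated, when it could come from capture alone. The interim efficacy and futility analyses use the same observed outcome, and the sample size allows for non-participation but not for a capture gap.

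**Working it through.** **Inputs from the protocol (Sample size).** Usual care 20%, intervention 14%, 80% power, α = 0.05, total 1230; 10% non-participation; final total 1520, or 760 per arm.

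**Reproducing the plan's figures.** Two-sided test of two proportions with pooled null variance and no continuity correction:

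n per arm = [1.96·√(2p̄(1−p̄)) + 0.8416·√(a(1−a) + b(1−b))]² / (a−b)²

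With a = 0.20 and b = 0.14 this gives 614.1, rounded up to 615, so 1230 in total, as stated. For non-participation, 1230/0.9² = 1518.5, in line with 1520. The diluted intervention rate is 0.9 × 14% + 0.1 × 20% = 14.6%, and power at 760 per arm for 20% versus 14.6% is 79.5%. None of this is in dispute.

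**Assumed inputs.** Capture is the share of an arm's readmissions that occur at the 30 hospitals. The protocol gives no value. I use 90/95 and 85/95 (control/intervention, %), with the direction that the Discussion states.

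**Two readings of the 20%.**
- All-hospital: observed rate = true rate × capture, in each arm.
- In-system: 20% is already what the system sees in control, so observed control = 20% and observed intervention = true intervention rate × (intervention capture / control capture).

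**Rejection probability.** With SE₀ = √(2p̄(1−p̄)/760), SE₁ = √(a(1−a)/760 + b(1−b)/760) and d the observed difference, the probability of rejecting in the direction of d is Φ[(|d| − 1.96·SE₀)/SE₁].

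*Example, design benefit, 90/95, all-hospital.* Control 0.20 × 0.90 = 0.180; intervention 0.146 × 0.95 = 0.1387; d = 0.0413; SE₀ = 0.01878; SE₁ = 0.01875. (0.0413 − 0.0368)/0.01875 = 0.24, so power is 59%.

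*Example, no effect, 85/95, all-hospital.* Control 0.170; intervention 0.190; d = 0.020; SE₀ = 0.01971; SE₁ = 0.01970. (0.0200 − 0.0386)/0.01970 = −0.95, so rejection toward harm is 17.2%. Adding 0.15% toward benefit gives 17.4%.

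| Truth | Capture | Reading of 20% | Observed rates (%) | OR | Rejection |
|---|---|---|---|---|---|
| 20 vs 14.6 | full | either | 20.0 vs 14.6 | 0.68 | 79.5% |
| 20 vs 14.6 | 90/90 | all-hospital | 18.0 vs 13.1 | 0.69 | 74% |
| 20 vs 14.6 | 90/95 | all-hospital | 18.0 vs 13.9 | 0.73 | 59% |
| 20 vs 14.6 | 90/95 | in-system | 20.0 vs 15.4 | 0.73 | 65% |
| 20 vs 14.6 | 85/95 | all-hospital | 17.0 vs 13.9 | 0.79 | 39% |
| 20 vs 14.6 | 85/95 | in-system | 20.0 vs 16.3 | 0.78 | 46% |
| no effect | 90/95 | all-hospital | 18.0 vs 19.0 | 1.07 | 7.9% |
| no effect | 90/95 | in-system | 20.0 vs 21.1 | 1.07 | 8.4% |
| no effect | 85/95 | all-hospital | 17.0 vs 19.0 | 1.15 | 17.4% |
| no effect | 85/95 | in-system | 20.0 vs 22.4 | 1.15 | 20% |

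**When toward the null is correct.** Observed rate ratio = true rate ratio × (intervention capture / control capture). With a true benefit, the result stays between the truth and the null only while the capture ratio is below true control rate / true intervention rate. That limit is 20/14.6 = 1.37 at the design effect and 20/18 = 1.11 for a small benefit. The assumed ratios are 95/90 = 1.06 and 95/85 = 1.12. At 85/95 a true 20% versus 18% therefore just crosses the null: the OR moves from 0.88 to 1.01.

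**The case against.** The protocol discloses the limitation openly: no claims data, 30 hospitals only, a difference expected, and the reason for it. It does not say that the bias can run only toward the null, and for the effect that the trial is designed to detect its direction is right. This stands, and it limits the point to a missing condition, not a hidden flaw.

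A reader might go further and infer that the claims of nondifferential assessment and no missing data are false. The documents do not support that. The first is tied to using only routinely collected data in both arms. The primary outcome is itself defined by the 30 hospitals, so an outside admission can be read as a non-event under that definition. Both statements can hold for the outcome as defined. They mislead only if carried over to readmission anywhere.

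The power loss is also open to challenge. Sample size says the historical data covered only the narrower single-site definition, so 20% may already exclude outside admissions, and discounting it again would count the loss twice. This is why two readings are shown. Even on the all-hospital reading, equal 90% capture alone lowers power to 74%, so not all of the fall to 59% comes from the difference between arms.

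A further tempting inference is that deaths at home are counted as successes and could pass for benefit. The coding rule would score a death without a visit as not readmitted, but the document does not discuss deaths after discharge. Their handling may sit in an analysis plan not shown, and vital status is not among the items listed under Data collection. That is silence, not a stated error.

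**Conclusion.** The point holds as a wrong unconditional statement of direction. Given the protocol's own expectation and coding rule, the bias is against the intervention. It is toward the null only when the program is beneficial and the capture ratio stays below the true control-to-intervention rate ratio; with no true effect it produces apparent harm.

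At assumed capture of 90/95 and 85/95, power at the design effect falls from about 80% to 59–65% and 39–46%. Two-sided rejection under no effect rises from 5% to about 8% and 17–20%, nearly all toward harm. These sizes depend on capture values that the document does not give and on the reading of the 20%. The direction depends on neither. The correction is worth making because it changes what a null or adverse result can support.

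**What to change.** 1. In the Discussion's limitations paragraph, say that the expected difference biases the results against the intervention, and toward the null only if the program is beneficial.
2. In Outcomes and Analysis, limit the statements on nondifferential assessment and absence of missing data to readmissions within the 30 hospitals.
3. Prespecify a tipping-point sensitivity analysis of the primary result. Vary capture separately by arm over a stated range, for example 80% to 100%, correct the observed rates for it, and report the capture gap at which the conclusion changes. This needs only the observed counts and the assumed capture values.
4. Secondary and optional: where deaths are recorded in the system, report them by arm and add 30-day readmission or recorded death as a sensitivity outcome. Deaths outside the system would remain partly unseen.

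The cost is a more guarded limitations statement and a small amount of extra analysis. The design, sample size and primary model do not change.
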